#### Recruitment, screening, and enrollment

This study recruits in a Midwestern state of the United States. We will recruit using a variety of strategies such as referrals by local Alzheimer’s Association chapter, medical centers, and health care providers, study presentations, advertisement, websites, conference exhibits, and press release. Ninety subjects will be enrolled over a 5-year period using the inclusion/exclusion criteria (Table 1). Respondents to our recruitment will undergo a 4-step screening process to qualify for the non-MRI part of the study:Phone screen (5 to 10 minutes) to elicit AD diagnosis and contraindications to exercise;In-person interview (2 hours) at the CTSI to obtain informed consent/assent and Health Insurance Portability and Accountability Act (HIPAA) and medical record release authorization. Then, two staff will take turns to interview the subject and family caregiver separately. For example, an RA will first interview the subject using the MMSE and health history form, while the study coordinator will interview the family caregiver using the CDR. Afterwards, the RA will interview the caregiver using the health history form, while the study coordinator will interview the subject using the CDR and conduct a focused neurologic and cardiac physical exam;Medical verification of AD diagnosis, exercise safety, and MRI safety with the subject’s health care providers (1 to 4 weeks). Medical verification letter will be sent if the subject’s CDR is 0.5 to 2 and MMSE is 15 to 26; andSymptom-limited peak cycle-ergometer test (30 to 60 minutes) to rule out cardiac ischemia and serious arrhythmia and determine peak heart rate (HR) and maximal oxygen consumption (VO_2peak_). The test is conducted either by a trained exercise technician, a study staff/RA, and a physician co-investigator, or a trained exercise technician, a study staff/RA, and an allied health professional trained in supervising exercise testing with the physician on call.

Subjects who pass all four steps will be considered ‘tentatively enrolled’ if they are willing to undergo MRI with MRI safety verification in step 3 above, or ‘enrolled’ if they refuse to participate in MRI or without MRI safety clearance in step 3 above. Tentatively enrolled subjects will be further screened for MRI eligibility using the Volunteer Safety Screening questionnaire mandated by the Center for Magnetic Resonance Imaging, and undergo baseline MRI if deemed safe. Subjects whose scans meet the following criteria will be notified to pursue medical evaluation with their providers and excluded from the study: normal pressure hydrocephalus, brain tumor, subdural hematoma, significant post traumatic encephalomalacia, one or more large hemispheric infarctions. Subjects whose scans do not meet those MRI exclusion criteria will be formally enrolled in the study.The subject timeline is depicted in Figure 2. The actual date of enrollment of the first subject was 3 June 2014.

**Figure 2 Fig2:**
[figure not shown]
**Subject flow and timeline.**

#### Data collection

Enrolled subjects will be scheduled to complete baseline data collection (about 3 hours). Subsequent data collection will occur at 3, 6, 9, and 12 months for cognition and other outcomes, which are further described under ‘Variables and Their Measures’ and in Figure 2. Subjects who undergo MRI at baseline will be re-evaluated for eligibility for MRI at 6 and 12 months (Figure 2). The first five data collections will be double checked by co-investigators and serve as further training for data collectors. Data collected by one assessor will be separately scored and entered into the study database by another assessor. Data collectors will not interact with enrolled subjects except for data collections.

#### Participation in the cycling or stretching exercise

Within two weeks of completing baseline data collection, the subjects will start their assigned exercise. Cycling or stretching exercise consists of a total of 72 sessions that will be provided 3 times a week for 6 months. The 72 sessions will be delivered over a 27-week period to account for the 3-month data-collection week (no exercise sessions) and accommodate vacation and illness make-ups. A trained exercise interventionist will lead each exercise session and supervise up to three subjects. In each session, subjects will do a 5-minute cardiac warm-up and cool-down before and after cycling and stretching exercises following the American College of Sports Medicine’s guidelines [51]. Hence, the session durations will gradually lengthen from 30 minutes to 60 minutes as subjects progress from 20 to 50 minutes of cycling at moderate intensity or stretching at low intensity over time. Upon arriving in each session, the exercise interventionist will assist subject’s placement of a Polar™ Wireless HR Monitor (RS400, Lake Success, NY, USA) for continuous HR monitoring. Resting HR and blood pressure will be taken. During cycling or stretching exercise, subjects will rate their Rating of Perceived Exertion (RPE) on the 6 to 20 Borg RPE scale every 5 minutes and corresponding HR will be documented. Blood pressure will be measured every 10 to 15 minutes, while talk test and overexertion signs and symptoms will be continuously monitored. Subjects can leave the site after their HR and blood pressure return to pre-exercise levels.

#### Cycling

For subjects whose HR reserve can be accurately derived from the symptom-limited peak cycle-ergometer test, we will prescribe moderate intensity exercise as 50 to 75% of HR reserve (HR reserve = peak HR-resting HR). Test-rest reliability will be established for the first ten subjects who volunteer to go through the test twice within 1 week at baseline. For subjects whose HRs cannot be used to derive HR reserve due to HR-altering drugs or irregular heart rhythm, moderate-intensity exercise will be prescribed as 9 to 14 on the 6 to 20 Borg RPE scale. The proper use of the RPE will be continuously reinforced during exercise. Therefore, for session 1, cycling intensity will be set at 50 to 55% of HR reserve or RPE 9 to 11 for 20 minutes. Cycling intensity and duration will be alternatively increased by 5% of HR reserve (or 1-point on the RPE) or 5-minute increments as tolerated up to 70 to 75% of HR reserve (or RPE 12 to 14) for 50 minutes a session over time (Table 2).

**Table 2 Tab2:** **Cycling and sham exercise prescription and progression**

Week	Cycling intensity		Sham exercise intensity		Duration (minutes)
	% of HR reserve	RPE	% of HR reserve	RPE	
1	50 to 55%	9 to 11	10 to 20%	7 to 8	20 to 30
2	50 to 55%	9 to 11	10 to 20%	7 to 8	30 to 40
3	55 to 60%	10 to 12	10 to 20%	7 to 8	30 to 40
4	55 to 60%	10 to 12	10 to 20%	7 to 8	40 to 50
5	60 to 65%	12 to 14	10 to 20%	7 to 8	40 to 50
6	60 to 65%	12 to 14	10 to 20%	7 to 8	50
7	65 to 70%	12 to 14	10 to 20%	7 to 8	50
8	65 to 70%	12 to 14	10 to 20%	7 to 8	50
9	70 to 75%	12 to 14	10 to 20%	7 to 8	50
10	70 to 75%	12 to 14	10 to 20%	7 to 8	50
11 to 24	70 to 75%	12 to 14	10 to 20%	7 to 8	50

*Abbreviations:*
*HR* heart rate, *RPE* Rating of Perceived Exertion.

Durations do not include warm-up and cool-down periods (10 minutes).

#### Stretching exercise

Stretching exercise will not exceed 20% of HR reserve or RPE 8 and will include primarily seated movements and static stretches. Stretching exercise will begin seated with very slow and deliberate calf raises, knee extensions, knee lifts, elbow flexion, shoulder abduction, and shoulder shrugs. Thereafter, stretches will be performed as follows: seated static calf stretch; seated anterior tibialis stretch; seated triceps stretch; seated deltoid stretch; assisted seated pectoralis major stretch; seated trapezius stretch; seated neck lateral rotation (looking over shoulder slowly); seated piriformis stretch; and standing calf stretch using chair for balance. There will be a minimum 2-minute rest between stretches. The number of repetitions and durations for each stretch will be gradually increased to match the session duration of cycling (Table 2).

#### Treatment fidelity

This study was designed to ensure treatment fidelity based on the National Institutes of Health Behavioral Change Consortium recommendations [52]. The co-investigators such as the exercise physiologist will assess treatment fidelity on all session case reports via weekly meeting with the exercise interventionist and conduct in-person fidelity check in 2% of randomly selected exercise sessions using a standard form. The exercise interventionist will be re-trained as needed.

#### Exercise safety, modification, retention, adherence, and validation

Safety is the cornerstone for increasing exercise adherence and retention. As previously described, we have built-in approaches to ensure subject safety, such as the 4-step safety screening, exercise prescription based on the cycle-ergometer testing to individualize exercise prescription and progression, exercise supervision, and continuous monitoring of exercise responses (HR, blood pressure, RPE, talk ability, signs, and symptoms). Exercise adherence will be documented on the session case report forms to indicate if and what aspects of the prescription are or are not met and why. We will build in nine program-level and six staff-level strategies to improve retention and adherence (Table 3). The success of the intervention delivery will be further validated using aerobic fitness measures described below.

**Table 3 Tab3:** **Adherence and retention plan**

Program-level strategies:	
1	Individualize exercise program to improve enjoyment and comfort
2	Monitor subject reactions during exercises to ensure safety
3	Exercise at sites convenient for subjects
4	Provide transportation to all study activities
5	Keep individual exercise diaries that subjects can share with families
6	Reimburse gym membership fees (will be prorated)
7	Collect data on separate days during each data-collection week (<2 hours/day)
8	Allow make-ups for vacations and illness
9	Compensate subjects (will be prorated)
**Staff-level strategies:**	
1	Know the person (for example, routine, personality, likes, dislikes, and communication patterns)
2	Guide subjects with sensitivity
3	Frequent communications with family caregivers and health care providers (for example, provide progress summary letters for upcoming doctor appointments)
4	Address unmet needs to reduce BPSD
5	Focus on achievement and progress
6	Establish rapport from day 1

*Abbreviation:*
*BPSD* behavioral and psychological symptoms of dementia**.**

### Variables and their measures

#### Primary outcome

Cognition will be measured using the ADAS-Cog as described by Rosen *et al*. [53]. The ADAS-Cog is widely used in AD drug RCTs with well-established norms [48]. It assesses orientation, memory, recall, language, and praxis with a total score of 0 to 70 (higher score = worse function). The ADAS-Cog’s interrater reliability is 0.65 to 0.99 and test-retest reliability is 0.51 to 1.0 [53]. In this pilot RCT, the ADAS-Cog will be administered at baseline and at 3, 6, 9, and 12 months.

#### Secondary outcome

Hippocampal volume will be determined at baseline and 6 and 12 months using the same 3 Tesla-B (3 T-B) Prisma system (Siemens, Erlangen, Germany) by the technician of the Center for Magnetic Resonance Imaging. The technician is blinded to the study aims, subject group assignments, and previous scans. The sequence includes Magnetization Prepared Rapid Gradient Echo Imaging (MPRAGE) (approximately 5 minutes), Fluid Attenuated Inversion Recovery (FLAIR) (approximately 3 minutes), and resting Blood Oxygen Level Dependent Signal (BOLD) (approximately 10 minutes). The Aging and Dementia Imaging Research Laboratory at Mayo Clinic will assist the installation and qualification of this sequence on the 3 T-B system following the same procedures established for multiple multisite studies [34]. MRI data will be transferred securely to the Mayo Clinic. The Mayo Clinic will perform quality control of each incoming image file for protocol verification, image quality, and identification of medically significant findings. The MRI will generate different measures of brain volume:Change in hippocampal volume over time (measured using longitudinal Free Surfer V5.1 [54, 55]). Hippocampal volume is perhaps the most widely used morphometric measure in the AD literature [56]. Hippocampal volume rate of change is the primary volume measure;Boundary Shift Integral (BSI) measures of change in brain volume over time [57–59]; and;BSI measures of change in ventricular volume over time. BSI measures of brain and ventricle are global measures that do not require any *a priori* assumptions about where in the brain the effect of the intervention might be manifested [60, 61].

#### Other outcomes

This pilot RCT will inform a future full-scale RCT about potential outcomes that might be more sensitive to aerobic-exercise intervention: discrete cognitive domains; exercise adherence; aerobic fitness; physical function; BPSD; and medical changes (Table 4). Discrete cognitive domains include attention, processing speed, executive function, memory, and language. Each domain will be measured using instruments established in the AD Centers’ Uniform Data Set. Attention will be measured with Wechsler Digit Span. Processing speed will be measured with Wechsler Digit Symbol and Trial Making Test (TMT) Part A. Executive function will be measured using TMT Part B, Executive Interview-25 (EXIT-25) [62], Behavioral Dyscontrol Scale (BDS) [63] and Executive Clock Drawing Test (CLOX) [64]. Memory will be measured with Wechsler Memory Scale-Revised Logical Memory Story A and B Immediate and Delayed Recalls. Language will be measured with Animal and Vegetable Verbal Fluency and Boston Naming Test [65]. Exercise adherence will be calculated as: 1) the percent of the attended sessions divided by 72 for each subject; and 2) the percent of the attended sessions in which a subject meets the session prescription divided by the total attended sessions. Aerobic fitness will be measured by the symptom-limited peak cycle-ergometer [51, 66] and shuttle-walk [67], and the 6-minute walk test [68], Physical function [69] will be measured by Short Physical Performance Battery (SPPB) [70], and Disability in AD (DAD) scale [71]. BPSD will be measured by the Neuropsychiatric Inventory-Caregiver (NPI-Q; [72, 73]), Alzheimer’s Mood Scale (AMS) [74], and Cornell Scale for Depression in Dementia (CSDD) [75]. Medical changes include changes in medical conditions, falls, medications, and health care service use and will be tracked at each exercise session. An RA will code medical changes in the previous 3 months at each data collection.

**Table 4 Tab4:** **Variables assessed at specific times (S: screening, M: month)**

Variables	Measures	S	M0	M3	M6	M9	M12
Primary outcome							
Global cognition	ADAS-Cog		x	x	x	x	x
Secondary outcome							
Brain volumes							
Hippocampal volume	MRI		x		x		x
Brain volume	MRI		x		x		x
Ventricle volume	MRI		x		x		x
Other outcomes							
Discreet cognitive domains							
Attention	Digit Span (Wechsler)		x	x	x	x	x
Processing speed	Digit Symbol (Wechsler)		x	x	x	x	x
	TMT Part A						
Executive function	TMT Part B		x	x	x	x	x
	EXIT-25						
	BDS Executive Clock Drawing test						
Memory	Logical Memory Story A and B		x	x	x	x	x
	Immediate Recall						
	Delayed Recall						
Language	Verbal Fluency		x	x	x	x	x
	Animal						
	Vegetable						
	Naming						
	Boston Naming Test						
Exercise adherence	Percent	Every exercise session					
Aerobic fitness	Symptom-limited peak cycle-ergometer test,	x		x	x	x	x
	Shuttle-walk test, 6-minute walk test		x	x	x	x	x
Physical function	SPPB, DAD		x	x	x	x	x
BPSD	NPI-Q, AMS, CSDD		x	x	x	x	x
Medical changes	Medical diagnoses, falls, medications, and health care service use	Monthly					
Covariates							
AD stage	CDR, MMSE	x					
Demographics	Age, education, gender, race	x					
Premorbid intellect	WTAR		x				
Unsupervised physical activity	PASE, actigraph	Monthly					

*Abbreviations:*
*AD* Alzheimer’s disease, *ADAS-Cog* Alzheimer’s Disease Assessment Scale-Cognition, *AMS* Alzheimer’s Mood Scale, *BDS* Behavioral Dyscontrol Scale, *BPSD* behavioral and psychological symptoms of dementia, *CDR* Clinical Dementia Rating, *CSDD* Cornell Scale for Depression in Dementia*, DAD* Disability in Alzheimer’s Disease scale, *EXIT-25* Executive Interview-25, *MRI* magnetic resonance imaging, *MMSE* Mini-Mental State Examination, *NPI-Q* Neuropsychiatric Inventory-Caregiver, *PASE* Physical Activity Scale for the Elderly, *SPPB* Short Physical Performance Battery, *TMT* Trail Making Test, *WTAR* Wechsler Test of Adult Reading*.*

#### Covariates

We selected covariates that have been linked to exercise effects such as AD stage, demographics, premorbid intellect, and unsupervised physical activity (Table 4). However, the selected covariates are not meant to be all-inclusive. AD stage will be assessed using the CDR and MMSE during screening and verified during AD consensus diagnosis. Demographics include age, gender, race, and education and will be collected during screening. Premorbid intellect will be assessed at baseline using the Wechsler Test of Adult Reading (WTAR) [76]. Unsupervised physical activity will be measured by the Physical Activity Scale for the Elderly (PASE) ([77, 78] and actigraph monthly for 7 days.

### Data management

#### Data entry, coding, and storage

The principal investigator (PI) and statistician will oversee data management to ensure data accuracy and completeness. All data forms will be de-identified with paper copies double locked and entered into the username- and password-protected electronic database in Research Electronic Data Capture (REDCap). A coding book is generated in REDCap once the database is set up. REDCap is a secure web interface with data checks during data entry and uploading to ensure data quality, and is housed on secure servers operated by the University of Minnesota Academic Health Center’s Information Systems. Data collection forms returned to the research office by the RAs will be reviewed by the study coordinator for completeness. Data entry will occur only after verified data completeness.

#### Data audits

Data audits of electronic outcome data will be conducted by the PI. If the PI identifies any discrepancies in scoring between the RA who collected data and the RA who entered data, the RAs need to consult the neuropsychologist co-investigator for correct scoring and the correct scores will be documented on paper and entered into REDCap.

#### *Data and safety monitoring board* (*DSMB*)

The DSMB will be comprised of three senior scientists from the University of Minnesota who are independent of our study and will have no direct involvement with the study. The DSMB will approve the study protocol and subsequent modifications, monitor and review subject and data safety and confidentiality, subject accrual and retention, adherence to inclusion and exclusion criteria, adverse events, data quality, management, and analysis, and study progress. The DSMB will also monitor the ongoing integrity of the study and review any preliminary data analyses prepared by the statistician and annual reports. The DSMB will meet by teleconference initially, following the collection of some 3-month data, and semi-annually.

### Statistical analyses

All variables will be assessed using the appropriate descriptive statistics, means and standard deviations (SD), medians, ranges, and frequencies. This approach will also allow evaluation of patterns of missing values and distribution of data. Analysis will be accomplished using SAS.

#### Aim 1: determine the immediate effect of the cycling intervention on cognition in Alzheimer’s disease

The primary comparison for both hypotheses in Aim I will be a 2-sided test of the overall mean in a 1-way ANOVA with age stratum as the factor and the change in ADAS-Cog from baseline to 6 months as the response against the null hypothesis value of 3.2 points, which is the mean 6-month increase in ADAS-Cog in pooled placebo groups of AD drug RCTs (n = 534) [48]. Separate ANOVAs will be run for each randomization group. Because we stratified treatment assignment (by age) in the design of the study, it is important that we account for this in the analysis of the trial data in order to realize the improved power of this design. Missing values at 6 months will not be imputed by last-observation-carried-forward because this would bias the mean change toward zero. Further analysis will use an analysis of covariance (ANCOVA) to determine significant difference in ADAS-Cog between groups at 6 months after adjusting for other covariates, including baseline ADAS-Cog and age stratum as covariates. Other covariates and potential outcome variables at baseline (Table 4) will be screened for possible inclusion in the model if any are associated with ADAS-Cog at a *P* < .1 level.

Additionally, we plan to model the longitudinal trajectory of ADAS-Cog measured over the first 6 months (and then subsequently over the first 12 in Aim II). The trajectory of ADAS-Cog measures over time will first be assessed using individual subject’s scatterplots and line graphs of the ADAS-Cog plotted together over time. This analysis will help to determine the appropriate function of time to model the outcome. A mixed-effects model of the ADAS-Cog measures will then be fit with fixed-effects for treatment group, (a function of) time, and their interaction and random subject-specific intercepts and slopes. The mixed-effects model will allow us to estimates of average rates of change in ADAS-Cog between the two treatment groups and assess variability in the rates of change between subjects. Mixed-effects models are advantageous because they directly accommodate correlated observations, which are expected in repeated measures, and deal readily with missing data. Additionally, we will consider longitudinal mixed-effects models with fixed-effect covariates identified in the ANCOVA and their interaction with time and treatment group. This will allow us to assess whether or not the changes in cognition and the effect of treatment group are moderated by other covariates.

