### Sample size

The primary endpoint is the 6-month within-group change in the ADAS-Cog, compared with the mean increase of 3.2 points from pooled placebo groups in AD drug RCTs with a total sample size of 534 (assuming equal numbers of mild and moderate AD subjects) [48]. Power calculations were based on a one-sample *t-* test (2-sided) at the 0.05 level, using the pooled standard deviation (SD) = 6.25 from the same placebo groups in AD drug RCTs [48]. Sample size was further determined by factoring in 16% attrition, which was based on the attrition rates from our previous studies [19, 20], 12 to 41% attritions in AD drug RCTs [49], and 0 to 41% attritions in non-AD exercise RCTs [12]. As a result, we will enroll 90 subjects and randomize 60 to the cycling group and 30 to the control group. The power calculation is conservative as it does not account for the stratified randomized design (or equivalently assumes that there is no difference between the strata, see below).

If 50 subjects in the exercise group complete the 6-month measurement, then the study has 80% power to detect a difference of at least 2.5 points with a one-sample 2-sided *t*-test at the 0.05 level. That is, if cycling leads to a true mean increase in the ADAS-Cog of no more than 0.7 points, the study will have 80% power to detect a difference from the increase of 3.2 observed in placebo groups in AD drug RCTs. In our control group, if 25 complete the trial, then the expected half-width of the 95% confidence interval for the mean 6-month change in the control group is 2.4. Although there is little power to detect a difference between our controls and the placebo groups in AD drug RCTs, our trial will provide a valuable estimate of the intervention’s Hawthorne effect.

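### The primary 6-month test is in effect a complete-case analysis that ignores the month-3 ADAS-Cog; if faster decliners drop out, it can favour cycling against the fixed 3.2

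*Protocol article*

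**What the plan says.** The Sample size section defines the endpoint: "The primary endpoint is the 6-month within-group change in the ADAS-Cog, compared with the mean increase of 3.2 points from pooled placebo groups". Under Aim 1 in Statistical analyses, the primary test is a two-sided test of the overall mean in a one-way ANOVA by age stratum, run separately in each arm, with the baseline-to-6-month change "as the response against the null hypothesis value of 3.2 points".

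On missing data, Aim 1 says: "Missing values at 6 months will not be imputed by last-observation-carried-forward because this would bias the mean change toward zero". It names no other method for the primary test. The power statement counts subjects with the 6-month score: "If 50 subjects in the exercise group complete the 6-month measurement, then the study has 80% power".

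The ADAS-Cog is also measured at 3 months (Primary outcome; Table 4). A mixed-effects model over the first 6 months would use that score, and the protocol says of such models: "Mixed-effects models are advantageous because they directly accommodate correlated observations, which are expected in repeated measures, and deal readily with missing data". That model is introduced as an additional analysis, not as the primary test.

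**The concern.** An ANOVA on the 6-month change can use only subjects who have a 6-month score. Once LOCF is excluded and nothing replaces it, what remains is the mean among completers. If subjects on a steeper decline are more likely to miss the 6-month visit, completers decline less than all randomised subjects, and the cycling mean moves towards zero and below 3.2. The protocol rejects LOCF because it does exactly this.

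In a comparison between randomised arms, similar dropout in both arms would cancel at least part of such a bias. Here each arm is tested alone against a constant, so nothing in the control arm can offset it. At stake are the size of the primary estimate and the false-positive rate of the test that carries Hypothesis 1a.

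**Working it through.** **Inputs from the protocol (Sample size; Aim 1)**

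- Null value 3.2; "test (2-sided) at the 0.05 level".
- SD of the 6-month change: "using the pooled standard deviation (SD) = 6.25 from the same placebo groups in AD drug RCTs".
- 60 randomised to cycling, 16% attrition, 50 completers.
- Target difference 2.5, that is, "if cycling leads to a true mean increase in the ADAS-Cog of no more than 0.7 points".

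**Step 1. Reproduce the plan's own figures**

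- Enrolment: 50 / (1 − 0.16) = 59.5, so 60. Agrees.
- Standard error: 6.25 / √50 = 0.884.
- Power, normal approximation: Φ(2.5/0.884 − 1.96) = Φ(0.868) = 80.7%. By noncentral t with 49 degrees of freedom it is 79.2%. The stated 80% is reproduced.

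**Step 2. Bias of a completer mean**

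Let d be the share lost, C the completer mean, and Δ the mean change in dropouts minus that in completers. The all-randomised mean is (1 − d)·C + d·(C + Δ) = C + d·Δ, so the completer mean is off by −d·Δ. The protocol gives no value for Δ, so a range is shown. The true cycling mean is set to 3.2 (no effect), and 3.2 is taken as free of dropout bias. The favourable rejection rate is the lower-tail rejection probability from the noncentral t with n = 50 and SE 0.884.

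| d | Δ (assumed) | Bias | Favourable rejection (nominal 2.5%) |
|---|---|---|---|
| 0.16 | 0 | 0 | 2.5% |
| 0.16 | +1.6 | −0.26 | 4.7% |
| 0.16 | +3 | −0.48 | 7.7% |
| 10/60 | +3 | −0.50 | 8.0% |
| 0.16 | +5 | −0.80 | 14.2% |
| 0.16 | −3.2 | +0.51 | 0.6% |

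**Step 3. Scale against the LOCF bias that the plan rejects**

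Suppose one sixth are lost at random and a month-3 change of 1.6 (assumed, half of 3.2) is carried forward. LOCF is then off by −(3.2 − 1.6)/6 = −0.27. The completer mean is off by the same amount when dropouts decline 1.6 points more than completers: −1.6/6 = −0.27.

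**Step 4. What the month-3 score recovers**

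One arm of 60 was simulated 8,000 times with one-sixth dropout and a true mean of 3.2. Assumptions not in the protocol: 3-month change with mean 1.6 and SD 4.5, and correlation 0.4 to 0.8 with the 6-month change.

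| Dropout depends on | Odds ratio per SD of worsening | Completer bias | Completer favourable rejection | Likelihood with month 3: bias | Likelihood: favourable rejection |
|---|---|---|---|---|---|
| 3-month change | 2 | −0.26 to −0.53 | 4.9% to 8.9% | about 0 | 2.4% to 2.6% |
| 3-month change | 3 | −0.40 to −0.80 | 6.5% to 15.0% | −0.01 to −0.02 | 2.5% to 3.0% |
| 3-month change | 0.5 | +0.27 to +0.52 | 0.6% to 1.3% | about 0 | 2.3% to 2.6% |
| Unseen 6-month value (correlation 0.6) | 2 | −0.67 | 11.3% | −0.43 | 6.7% |

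With a true mean of 0.7, random dropout and correlation 0.6, power is 79.3% for completers and 80.8% for the likelihood estimate. The change costs no power.

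**Step 5. If the 3.2 carries dropout bias of its own**

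The protocol cites 12 to 41% attrition in AD drug trials. Assume that 3.2 is itself a completer mean and that Δ = 3 in both settings. The benchmark is then off by −0.12 × 3 = −0.36 to −0.41 × 3 = −1.23, against −0.48 in this trial. The net bias runs from −0.48 + 0.36 = −0.12 (favouring cycling) to −0.48 + 1.23 = +0.75 (against it).

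**The case against.** **Complete-case is inferred.** The article never says that only completers are analysed and does not exclude other imputation, and an unseen analysis plan may name a method. That limits the wording. But the protocol does fix the primary model and does take a position on missing data, and its power statement counts those with the 6-month measurement. Complete-case is the natural reading.

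**The direction is not established.** A reader might infer that the primary estimate is biased towards benefit and that its type I error is no longer 5%. The documents do not support that. They do not say that subjects who miss the 6-month score decline faster. The only related pattern they suggest is by age (Discussion: younger subjects may complete more of the exercise), and age stratum is already in the ANOVA. Stopping exercise is also not the same as missing an assessment, and Table 3 sets out retention measures. This objection stands: the bias is conditional.

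**The benchmark may be biased too.** This is the strongest objection. How the 3.2 treated dropout is not stated, and Step 5 shows that the net bias could run either way. If 3.2 is a completer or LOCF figure, testing an all-randomised estimate against it compares unlike quantities. This stands, and the fix has to say so.

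**A mixed model is already planned.** It uses the month-3 score over the same 6 months. As described, though, it is additional, takes its time function from inspection of plots, and lists no age-stratum term among its basic fixed effects. It does not yet supply the primary estimate.

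**Conclusion.** The point holds in conditional form. As written, the primary test is in effect complete-case and omits a score that the trial collects. If faster decliners drop out, the cycling mean can be too low by about 0.5 points, one fifth of the 2.5-point target, with favourable rejection of about 8% instead of 2.5%. Those figures assume about 16% loss, dropouts declining 3 points more than completers, and a 3.2 free of dropout bias. They illustrate sensitivity and do not estimate this trial's error rate. Random dropout gives no bias, the opposite pattern biases against cycling, and the net bias against 3.2 is unknown. The change is worth making because the alternative uses data already planned and loses no power.

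**What to change.** Make the primary 6-month mean change a likelihood-based repeated-measures estimate from all baseline, month-3 and month-6 ADAS-Cog scores of all randomised subjects. Fix in advance:

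- time as categorical visits, not a function chosen from plots;
- age stratum as a term;
- the 6-month contrasts, both against 3.2 and between the groups.

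Keep the completer ANOVA as a sensitivity analysis. Add a sensitivity analysis for dropout that depends on unseen values, for example one that shifts the dropouts' mean over a stated range of Δ. State that the comparison with 3.2 depends on how the historical figure treated dropout, and report that treatment if it can be established.

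Cost: a change of wording and slightly more analysis work, with no new data. Some bias remains if dropout depends on unseen scores (−0.43 of −0.67 in the scenario above), and the month-3 score cannot help for subjects lost before month 3.
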